### Primary outcome measures

#### Aerobic fitness

To assess aerobic fitness a submaximal exercise aerobic fitness test will be performed. Participants will undertake up to 4 × 5-min leg cycling using an isokinetic cycle ergometer, with resistance adjusted to elicit target heart rates equivalent to 45%, 55%, 65% and 75% of age-adjusted peak heart rate. Using ACSM metabolic equations [18], power output (W) and measured heart rate at each submaximal stage will be used to estimate submaximal oxygen consumption and VO_2_peak (ml•kg•min^-1^).

#### Energy expenditure

To quantify possible change of energy expenditure after the two exercise interventions, 12-hour energy expenditure will be assessed. At baseline, 3-month and 9-month post assessment participants will, on two days, wear a multi-sensor armband, Sensewear [16]. This small, lightweight self-contained device accurately measures and stores energy expenditure and physical activity data in the field.

#### Physical activity

The long, telephone version of the *International Physical Activity Questionnaire* (IPAQ) was adapted to measure the physical activity of adults with ID using proxy respondents [19]. To quantify possible change of physical activity via a simple recall questionnaire, the adapted version of the IPAQ, the IPAQ-ID, will be administered to carers of the adult with ID.

### Secondary outcome measures

#### Objectively assessed physical activity and sedentary time

Participants will wear an Actigraph GT1M/GT3X accelerometer (Actigraph, Pensacola, FL, US) on the right hip attached to an elastic belt, for 7 consecutive days. The Actigraph is a non-invasive device the size and weight of a matchbox that records activity counts and steps taken. Participants wear the accelerometer during waking hours except during water activities. The accelerometer data allows for checks of wearing compliance and can be used to estimate time spent in sedentary, light, moderate, and vigorous physical activities.

#### Intervention compliance

Compliance with physical activities in both intervention groups will be measured through a daily physical activity log. For participants in either intervention group the disability service provider staff will be asked to log each person’s participation in physical activities (type and duration).

#### Functional walking capacity

Participant’s functional walking capacity will be assessed through a 6-Minute Walk Test (6MWT). Participants will be asked to walk as fast as they can for 6 minutes and if required, the participant may briefly stop. The test will be performed indoors, along a flat, hard-surfaced passageway. The total distance walked will be measured and heart rate will be recorded using a heart rate monitor (Polar, Port Washington, NY, USA). This is a well validated test for a range of populations [20].

#### Participation in domestic activity

The 13-item Index of Participation in Domestic Life (IPDL) [21] scale will be administered to carers of the adult with ID. It measures participation in functional domestic activity, not physical activity.

#### Muscle strength

Isometric assessment of participants’ muscle strength will be via dynamometry and include maximal handgrip strength, biceps flexion, triceps extension and knee extension strength [22].

#### Body composition and body fat

The Innerscan Body Composition Monitor (Tanita BC-541, Tsimshatsui East, Kowloon, Hong Kong) will be used by a trained research assistant to measure the participant’s body mass and estimated percentage body fat. Height will also be measured. From the recorded information Body Mass Index (BMI) will be calculated.

#### Psychosocial measures

We will examine the effects of the interventions on attitudes and psychosocial outcomes through self-report and/or proxy interview data. Attitudes towards physical activity (self-efficacy, social support and exercise expectations) will be assessed using the following scales:

##### Self-Efficacy for Activity for persons with Intellectual Disabilities (SE-AID)

This scale [10] is a 6-item self-report scale with internal consistency (alpha) = 0.73, and test-retest reliability intraclass correlation (ICC) = 0.49.

##### Social Support for Activity for persons with Intellectual Disabilities (SS-AID)

This scale [10] has versions for closely related family and staff. The family version is a 7-item self-report scale with internal consistency (alpha) of 0.73, and test-retest reliability (ICC) of 0.79. The staff version has 6 items, with alpha = 0.74 and test-retest ICC = 0.78. The version of the scale administered will be dependent on the participants living circumstances.

##### The exercise perceptions scale

This scale [23] measures expected outcomes of exercise. It is a 9-item self-report scale (alpha = 0.81), and test-retest r = 0.72 [24].

Psychosocial outcomes (depression and health-related quality of life) will be assessed using the following scales:

##### The Glasgow Depression Scale (GDS)

The GDS [25] has self-report and proxy-report versions which correlate strongly (*r* = 0.93). It is specifically designed for people with ID and has excellent internal and test–retest reliability and criterion validity, with 96% specificity and 90% sensitivity. Both versions will be completed, with the proxy-report version being administered to the carers of the adult with ID.

#### Quality of life

##### The Health Utilities Index 2 (HUI 2)

This scale [26] used for economic evaluation will assess quality of life.

#### Health care costs

An economic evaluation will determine the cost-effectiveness of the intervention. To assess the impact on health economics carers of the adult with ID will be given a prospective diary to complete about the person’s use of health services. The diary will ask for information on the number of hospitalizations, any medical consultations (and other medical services) and any medications taken over the period.

The Health Utilities Index 2 (HUI 2) [26] is a widely used generic measure of health state utility used for economic evaluation. The scale will be administered to carers of the adult with ID.

### Statistical analyses

#### Sample size

We will power the study based on the primary outcome of aerobic fitness (VO_2_peak; ml•kg•min^-1^). Our MVI-Exercise approach is similar to a previous study that used a 12-week gym-based intervention for people with ID [27]. They reported substantially better post-test aerobic fitness outcomes (assessed by VO_2_peak) for the intervention group relative to controls (large effect size, Cohen’s d = 0.91). Assuming an effect size of d = 0.80 (equivalent to f =0.40), and using a design with three groups and three repeated measures, power calculations with alpha = 0.05, power = 0.95, and a correlation among repeated measures of 0.5 show that this would require a total sample size of 69 (i.e., 23 per group), to analyse between-group differences using repeated measures ANOVA. Our assumptions are conservative so as to avoid under-powering the study. Therefore, we will recruit 30 participants per group for a total sample of 90, which allows for 23% attrition without compromising power.

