#### Analyses

Repeated-measures ANOVA will be used to compare both the intervention and control group participants on primary and secondary outcome measures, at the 3-month and 9-month assessments. To identify personal characteristics of participants and features of their environment that are associated with better outcomes multiple regression will be used. Significance will be set to *p* < 0.05. Analysis will be on the basis of intention to treat, with a secondary per-protocol analysis.

For the economic evaluation a trial based cost-effectiveness analysis, taking a health system perspective, will compare the two exercise interventions with one another and, separately, with usual care (i.e., our control group). The economic evaluation will estimate the incremental cost-effectiveness of each of the interventions in terms of cost per quality adjusted life year gained. Participant level costs associated with use of health services and medications will be derived from proxy-reported utilisation at each follow-up and costed on the basis of standard published costs (e.g., Australian Refined Diagnosis Related Groups cost weights for hospitalisation and Medicare Benefits Schedule and Pharmaceutical Benefits Scheme [PBS] rates for medical services and prescribed medications respectively). Quality of life will be assessed by the HUI 2 via proxy and converted into health state utilities via the UK scoring system [28].

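### The sample size turns d = 0.80 into f = 0.40 with a two-group relation but uses it in a three-group ANOVA; if 0.80 is the largest gap among the three means, f is 0.33 to 0.38, so the stated power and attrition margin are too high and N = 69 is too low

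*Protocol article*

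**What the plan says.** The Sample size section powers the trial on VO2peak. It starts from an earlier 12-week gym-based study with better post-test fitness "for the intervention group relative to controls (large effect size, Cohen’s d = 0.91"). It lowers that value and converts it in one step: "Assuming an effect size of d = 0.80 (equivalent to f =0.40), and using a design with three groups and three repeated measures". With alpha 0.05, power 0.95 and a correlation of 0.5 between repeated measures, it arrives at 69 participants, 23 per group, for between-group differences in a repeated-measures ANOVA.

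Two statements rest on this result. The first is "Our assumptions are conservative so as to avoid under-powering the study". The second is that recruiting 90 gives a margin "which allows for 23% attrition without compromising power". The Analyses section names the same method: "Repeated-measures ANOVA will be used to compare both the intervention and control group participants on primary and secondary outcome measures". Neither section gives an expected mean for the lifestyle arm or a pattern for the three means.

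**The concern.** Cohen's f is the standard deviation of the group means divided by the within-group standard deviation. With two equal groups that ratio is half the standardised difference, so d = 0.80 gives f = 0.40. With three groups the ratio also depends on where the third mean lies, and a third mean inside the range pulls f below d/2. The protocol states the two-group equivalence and applies it to three groups in the same sentence.

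If the conversion is wrong, the effect actually powered is larger than the one stated. The 95% power at 69 completers then does not follow from d = 0.80, and neither does the 23% margin that supports 30 per group. A team relying on the paragraph would treat 69 completers at 9 months as fully powered.

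**Working it through.** **Inputs, all from the Sample size section:** k = 3 groups, m = 3 measures, r = 0.5, alpha = 0.05, target power 0.95, d = 0.80, f = 0.40, N = 69, 90 recruited.

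**Test.** Between-group factor of a repeated-measures ANOVA: noncentral F with df = (k − 1, N − k) and noncentrality λ = f² × N × m/(1 + (m − 1)r). Here m/(1 + (m − 1)r) = 3/2 = 1.5.

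**Reproducing the plan's figure.** With f = 0.40 and N = 69, λ = 0.16 × 69 × 1.5 = 16.56 and power is 95.5%. At N = 66 it is 94.5%, so 69 is the smallest balanced total. Other versions at f = 0.40 do not give 69: the group-by-time interaction needs 24, the within factor 18, one measure 102 and two measures 78. The attrition figure also follows: 1 − 69/90 = 23.3%. The step from f to N is therefore correct, and the error lies in the step from d to f.

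**Three-group conversion.** Let control be 0, exercise d, and lifestyle t × d with t between 0 and 1. Then

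f² = d² × (2/9) × (1 − t + t²).

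- t = 0 or 1: f = 0.80 × √2/3 = 0.377, the maximum within the range.
- t = 0.25 or 0.75: f = √(0.64 × 0.2222 × 0.8125) = 0.340.
- t = 0.5: f = 0.80/√6 = 0.327, the minimum.

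**Consequences**, with the full effect at every assessment and required N stepped in multiples of 3:

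| Lifestyle arm | f | λ at 69 | Power at 69 | Power at 90 | N for 95% | Loss allowed from 90 |
|---|---|---|---|---|---|---|
| Equal to control or exercise | 0.377 | 14.72 | 92.9% | 97.8% | 78 | 1 − 78/90 = 13.3% |
| Quarter or three-quarters of the way | 0.340 | 11.96 | 86.6% | 94.5% | 93 | none |
| Midway | 0.327 | 11.04 | 83.7% | 92.6% | 102 | none |

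**What f = 0.40 means in three groups.** The largest gap must be 0.40 × 3/√2 = 0.85 when lifestyle equals one of the other arms, and 0.40 × √6 = 0.98 when it is midway. The cited study reported 0.91.

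**The case against.** Four points can be made for the protocol.

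**The bound is conditional.** The paragraph never says that 0.80 is the range of all three means. If exercise exceeds control by 0.80 SD and lifestyle lies about 0.09 SD outside that interval, for example means of 0, 0.80 and 0.89, f does reach 0.40. This stands as a condition that must be stated. It does not rescue the text, which assumes no such pattern and offers the conversion as a plain equivalence.

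**The assumptions may still be conservative.** A reader might infer that the protocol's claim of conservatism is false. The figures do not support that in every pattern. When lifestyle equals control or exercise, f = 0.40 corresponds to d = 0.85, below the cited 0.91; with d = 0.91 in that pattern, f is 0.429, power at 69 is 97.6% and the required N is 60. Setting d = 0.91 and f = 0.40 in the formula above gives 1 − t + t² = 0.16/(0.8281 × 0.2222) = 0.869, so t is about 0.15. The claim fails only when lifestyle lies more than about 15% of the way in from either extreme. It needs qualifying, not deleting.

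**The practical effect is modest.** A reader might infer that the trial is underpowered. The calculation does not show that. Even midway, 80% power needs 66, fewer than the 69 left after the full planned loss, and at 90 power is 92.6% or more. What fails is the promise of 95% power after 23% attrition.

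**The corrected powers are conditional too.** They assume the full difference at all three assessments, one of which is baseline, before any intervention. That favours the plan, so the corrected figures should not be read as the trial's unconditional power.

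**Conclusion.** The equivalence is wrong as written. If 0.80 SD is the largest difference among the three means, f is 0.327 to 0.377. On the plan's own test, power at 69 completers is then about 84% to 93%, a shortfall of 2 to 11 points against the stated 95%. The 23% attrition allowance is likewise overstated: it is 13% in the best pattern and nil in the quarter-way and midway patterns. The required N of 69 is understated, since 78 to 102 completers are needed.

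This rests on two assumptions: the lifestyle mean lies within the control-to-exercise range, and the full effect is present at every assessment. The error is definite and reproducible, but it concerns the stated justification and does not by itself show that 90 recruits are too few.

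**What to change.** In the Sample size section:

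- Replace the conversion with the three-group values (f = 0.377 if lifestyle equals control or exercise, 0.327 if midway) and state which pattern of means is assumed.
- Restate power as about 84% to 93% at 69 completers and about 93% to 98% at 90, with both conditions in the same sentence: 0.80 is the range of the three means, and the full effect is present at every assessment.
- Replace the 23% allowance with at most 13% (78 completers) in the most favourable pattern, and none with lifestyle midway.
- Keep the sentence on conservatism but qualify it: in three groups, f = 0.40 corresponds to a largest difference of 0.85 to 0.98, against 0.91 in the cited study.

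Recruitment stays at 90 and no further data are needed. The only cost is a less favourable stated power and attrition margin.

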### Outcome assessments

All outcomes will be assessed at baseline, 3-months post-baseline and at 9-months post-baseline. Participants and assessors will be un-blinded. The primary outcome measures are aerobic fitness, energy expenditure and physical activity. Secondary outcomes include intervention compliance, participation in domestic activity, objectively assessed physical activity and sedentary time, muscle strength, functional walking capacity, health care utilisation and cost, quality of life, body composition and psychosocial measures.

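### The 95% power at N = 69 belongs to a group effect averaged over three visits including the randomised baseline, and is not shown for the planned 3- and 9-month comparisons

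*Protocol article*

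**What the plan says.** Under Sample size, the protocol article chooses one outcome for the calculation: "We will power the study based on the primary outcome of aerobic fitness". The effect comes from an earlier 12-week gym-based study in people with intellectual disability, described as similar to the structured exercise arm: "They reported substantially better post-test aerobic fitness outcomes (assessed by VO_2_peak) for the intervention group relative to controls", with d = 0.91. The planning value is lower: "Assuming an effect size of d = 0.80 (equivalent to f =0.40". The calculation is made "using a design with three groups and three repeated measures", with alpha 0.05, power 0.95 and a correlation of 0.5. It gives 69 in total, 23 per group, "to analyse between-group differences using repeated measures ANOVA". Recruiting 90 is said to absorb 23% attrition with power intact, and the section adds: "Our assumptions are conservative so as to avoid under-powering the study".

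Outcome assessments identifies the three measures: "All outcomes will be assessed at baseline, 3-months post-baseline and at 9-months post-baseline".

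Analyses states: "Repeated-measures ANOVA will be used to compare both the intervention and control group participants on primary and secondary outcome measures". It places those comparisons at the 3-month and 9-month assessments. It does not say which ANOVA term carries the conclusion.

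**The concern.** The source effect is a difference after treatment. The calculation attaches it to three measures, one of which is taken before treatment starts. A group main effect over those three visits averages in a baseline at which randomisation makes the expected difference zero, so the tested quantity is smaller than the assumed one. The questions the protocol asks, each approach against control and against the other at 3 and at 9 months, are different contrasts, and no power is stated for them.

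At stake is whether the 95% after attrition can be relied on, and whether a null result would be judged against a power the test did not have. The choice of ANOVA term also matters. An analyst who followed the sample size section and tested the three-visit main effect would be using the weakest of the omnibus tests considered here.

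**Working it through.** **Inputs.** From Sample size: f = 0.40, d = 0.80, three groups, m = 3 measures, rho = 0.5, alpha = 0.05, N = 69 (23 per arm) after attrition, N = 90 (30 per arm) recruited. From Outcome assessments: visits at baseline, 3 and 9 months. From Randomization: random allocation, hence zero expected baseline difference. My assumptions: equal correlations between visits, and the full effect kept at 9 months, which favours the plan.

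**1. Reproduce 69.** Group main effect: lambda = f² × N × m / (1 + (m − 1)rho), df = 2 and N − 3.
- N = 69: 0.16 × 69 × 3/2 = 16.56, power 0.955.
- N = 66: 0.16 × 66 × 3/2 = 15.84, power 0.945.

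So 69 is the smallest balanced N. Other terms with the same inputs do not give it: group-by-time 24, time effect 18, group effect over two measures 78, one-way ANOVA at a single visit 102.

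**2. Put zero at baseline.** With the full effect at two of three visits, f of the three-visit mean is 0.40 × 2/3 = 0.267.
- N = 69: lambda = 0.267² × 69 × 1.5 = 7.36, power 0.66.
- N = 90: lambda = 9.60, power 0.78.
- 95% would need about 150.

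In single-visit SD units, d = 0.80 becomes 0.53. The three-visit mean has SD sqrt(2/3) = 0.816, so its standardised effect is 0.65. The power figures use that smaller SD.

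**3. A separate input problem.** d = 0.80 equals f = 0.40 only for two groups. If 0.80 is the largest difference among three arms, arm means (0, 0, 0.8) give f = 0.377 and (0, 0.4, 0.8) give f = 0.327. Diluted main-effect power is then 0.60 and 0.48 at N = 69, and 0.73 and 0.60 at N = 90.

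**4. Omnibus tests aimed at follow-up.** Group-by-time: lambda = N × f² × (2/3)/(1 − rho), df = 4 and 2(N − 3), where 2/3 is the sum of squares of the time pattern (0, 1, 1) about its mean. Baseline-adjusted single visit: lambda = N × f²/(1 − rho²), df = 2 and N − 4.

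| Test | N | f = 0.40 | f = 0.377 | f = 0.327 |
|---|---|---|---|---|
| Main effect, zero at baseline | 69 | 0.66 | 0.60 | 0.48 |
| Group-by-time | 69 | 0.87 | 0.83 | 0.69 |
| Group-by-time | 90 | 0.95 | 0.92 | 0.82 |
| Single visit, adjusted | 69 | 0.93 | 0.90 | 0.79 |
| Single visit, adjusted | 90 | 0.98 | 0.96 | 0.89 |

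**5. Pairwise contrasts, d = 0.80.** Noncentrality = (d/s) × sqrt(n/2), where s is the residual SD in single-visit units.
- One visit, unadjusted, s = 1, df = 2n − 2: 0.76 at n = 23, 0.86 at n = 30.
- One visit, baseline-adjusted, s² = 1 − 0.25 = 0.75, df = 3n − 4: 0.87 at n = 23, 0.94 at n = 30.
- Mean of 3 and 9 months, baseline-adjusted: the mean has variance (1 + 0.5)/2 = 0.75 and covariance 0.5 with baseline, so s² = 0.75 − 0.25 = 0.50. Power is 0.97 at n = 23 and 0.99 at n = 30.

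**6. Lifestyle versus exercise.** The document gives no effect for this pair. If it were d = 0.4 (my assumption), the adjusted single-visit contrast has 0.34 at n = 23 and 0.42 at n = 30.

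**7. Sensitivity.** For rho from 0.3 to 0.8, with f = 0.40 and N = 69, diluted main-effect power runs from 0.76 down to 0.54. If only half the effect remains at 9 months, it is 0.37 (f = 0.377) or 0.29 (f = 0.327) at rho = 0.5.

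**The case against.** The strongest reply is that the trial is not badly sized. If d = 0.80 holds at both follow-ups and rho = 0.5, the baseline-adjusted mean of 3 and 9 months has 97% power with 23 per arm. With no attrition and f = 0.40 taken literally, group-by-time at N = 90 reaches 95%. This stands, so a reader who inferred that 95% is out of reach for any analysis of this trial would go too far. It does not rescue the statement as printed: the protocol claims 95% at 69 after attrition, and it plans comparisons at 3 and at 9 months without mentioning a pooled contrast.

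A second reply is that the Analyses section never commits to the group main effect. That is also right. The term is inferred from the sample size, by exact reproduction of 69. A reader might infer that the trial will be analysed at 48-66% power; the document does not say so, and group-by-time is an equally open reading of the plan. Part of the 48-60% range also comes from the conversion of d to f. Dilution alone gives 66%.

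Two other inferences are unsupported. Nothing in the document plans or claims equivalence of lifestyle and exercise, so a null result being read that way is only a possibility. Nor does the document rank 3 months above 9 months: the Abstract and Background give both equal standing.

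**Conclusion.** The point holds as a fault in the stated power and its justification. The arithmetic of 69 is correct for a quantity that includes an effect at the randomised baseline. With that effect set to zero, the same test has about 66% power rather than 95% at N = 69, and 78% at N = 90, using the protocol's own f. For the follow-up comparisons the protocol plans, 95% is not shown: at N = 69, 69-87% for group-by-time, and 76% (unadjusted) or 87% (adjusted) for a single-visit pairwise contrast. The word conservative is therefore not earned.

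These figures assume equal correlations of 0.5 and no loss of effect over the six staff-only months. They also grant d = 0.80, whose source is an exercise-versus-control study; the document offers no support for that value in the lifestyle arm, for lifestyle against exercise, or at 9 months. For a true d = 0.80, a baseline-adjusted analysis remains well powered at the planned size, so what must change is the named test and its stated power, not the number of participants.

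**What to change.** - Do not rest the VO2peak conclusion on the group main effect over three visits.
- Analyse the follow-up visits with baseline as a covariate or constrained equal across arms, by ANCOVA or a longitudinal mixed model.
- State which contrast is primary: 3 months, 9 months or their mean. The choice is the investigators'.
- Restate power for that contrast. For d = 0.80 and rho = 0.5 it is about 87% at 23 per arm (94% at 30) for a single visit, or about 97% at 23 per arm for the mean if d = 0.80 holds at both visits.
- Say that d = 0.80 is derived from an exercise-versus-control study, and give the smallest lifestyle-versus-exercise difference the trial can detect.

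The cost is wording in Sample size and Analyses and, for a single-visit contrast, a less favourable power statement. No new participants or data are needed.
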